### Control

Participants allocated to the control arm of the study gained access to a dynamic web page containing publicly available standardized informational resources about PrEP, including information on eligibility, use, side effects, effectiveness, access, and payment, as well as specific PrEP resources for transgender females. This web page also provides a list of alternative telehealth-based PrEP providers and contact information for community partners offering PrEP navigation in each geographic area.

The personal landing page for each participant was customized based on their study arm and subgroup (adolescent, adult transgender woman, or adult cisgender man who has sex with men). Participants allocated to the control condition could not access any of the PrEPTECH features, which were not displayed to them. A second panel on the control arm participants’ landing page shows what surveys they have taken and are currently eligible to take.

### Participant Timeline

The entire 6-month web-based study is completed on the PrEPTECH website. A sequential illustration of participants’ experiences is shown in Figure 1.

Recruited prospective participants review web-based materials on the PrEPTECH website and elect whether to create a web account, which requires them to verify their email address and phone number and provide their name.After creating an account, prospective participants are screened for eligibility via a web-based survey. Those meeting the inclusion criteria proceed to step 3.Each participant then verifies their identity by providing a photo of themselves with a photo ID card or a link to a public social media profile that shows their name with a visible photo of themselves.Participants who provide identity verification are invited to complete the baseline web-based survey.Each participant is randomized after baseline completion, informed of their assignment, and provided with standardized web-based resources on PrEP access or brought to the first step of the PrEPTECH intervention.All participants are invited to take the midpoint survey 90 days after the baseline survey.All participants are invited to take the final survey 180 days after the baseline survey.

**Figure 1 figure1:**
[figure not shown]
PrEPTECH study and intervention participant experience. *For adult men who have sex with men who are initially provided with a 30-day supply of free pre-exposure prophylaxis (PrEP), information and guidance on paying for PrEP (through insurance, patient access programs or self-pay) is provided concurrently with the provision of at-home laboratories and the initial telehealth appointment. Rx: prescription.

### Data Collection and Management

Study data come from surveys completed by participants at three time points, namely (1) before randomization (baseline); (2) 3 months (90 days) after enrollment; and (3) 6 months (180 days) after enrollment, as well as study implementation records that document participant follow-up activities and participant progress through the intervention. Additional study data come from the laboratory tests and medical intake forms collected before the provision of the first PrEP prescription and approximately 90 days later, completed by participants in the intervention arm.

All survey data are collected digitally and entered directly by participants via embedded surveys hosted by Qualtrics (Qualtrics International, Inc) into the PrEPTECH study website. For participants in the intervention arm, laboratory test and medical intake information is collected via myLAB Box (laboratory test) and an embedded survey hosted by Qualtrics (medical intake). Medication prescription information is transferred electronically, using DrChrono (EverCommerce), to Ridgeway Pharmacy.

Participants receive automated email and SMS text message reminders to complete all surveys, with additional customized follow-up via email and SMS text message from the study team. To maximize the response rate and study retention, participants are compensated with web-based gift cards for the completion of each survey: US $40 at baseline, US $50 at 3 months, and US $60 at 6 months.

Upon randomization, each participant was assigned a unique identifier used throughout the study. However, data will be associated with personal identifiers while the study is ongoing, as this is necessary for participant follow-up. Electronic data will be stored for 3 years after the conclusion of the study. All data relevant to the study will ultimately reside in ETR Associates’ Amazon Web Services system (Amazon Web Services, Inc) using Aptible (Aptible Inc) to ensure Health Insurance Portability and Accountability Act compliance.

### Outcomes

#### Primary Outcomes

PrEP initiation at 3 months after enrollment will be assessed using participant self-report of having taken at least one dose of PrEP medication between study enrollment and midpoint survey administration.

#### Secondary Outcomes

##### PrEP Initiation

PrEP initiation at 6 months after enrollment will be assessed using participant self-report of having taken at least one dose of PrEP medication at any point during the intervention period.

##### PrEP Persistence

PrEP persistence at 3 and 6 months after enrollment will be assessed using participant self-report of having taken at least one dose of PrEP medication during both the first and second 90-day periods of the intervention.

##### PrEP Adherence

PrEP adherence at 3 and 6 months after enrollment will be assessed through multiple measures. Continuous adherence will be assessed using participant self-report of the number of doses of PrEP taken in the past 30 days, excluding participants taking event-based PrEP, as adherence would need to be conceptualized differently for this approach to PrEP administration. Categorical adherence will be assessed using participant self-report of taking a dose of PrEP medication for at least four days per week, “all of the last 4 weeks (4 out of 4 weeks)” or “most of the last 4 weeks (3 out of 4 weeks),” excluding participants taking event-based PrEP.

##### PrEP Coverage

PrEP coverage at 3 and 6 months after enrollment will be assessed using participant self-report of the number of instances in the past 30 days of vaginal or anal sex in which there was no protection from event-driven PrEP (defined as taking PrEP between 2 and 24 hours ahead of the sex act and ≥2 doses 24 and 48 hours after the first dose), continuous PrEP (defined as taking a minimum of 4 doses of PrEP within a week of the sex act), or long-acting PrEP (defined as taking injectable PrEP within 2 months before the sex act).

##### PrEP Medication Prescription

PrEP medication prescription at 3 and 6 months after enrollment will be assessed through multiple measures, including self-report of having received a PrEP prescription at any point during the intervention, as well as documented medication prescription through study electronic health records (among eligible intervention arm participants only).

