### Recruitment and Randomization

To recruit potential participants, we contracted with an LGBTQ+ marketing and communications company to run paid advertising campaigns on social media platforms (eg, Facebook [Meta Platforms, Inc] and Instagram [Meta Platforms, Inc]) and LGBTQ+ dating apps (eg, Grindr [Kunlun Tech Co Ltd], Scruff [Perry Street Software Inc], Jack’d [Perry Street Software Inc], and Adam4Adam [A4A Network Inc]). The advertisements were targeted to the age and geographic eligibility criteria of the study and included a diverse array of men who have sex with men and transgender people, prominently featuring Black/African American and Hispanic/Latino individuals.

In addition to web-based recruitment, we identified community-based organization partners in each geographic location of the study and paid them to conduct web-based and in-person outreach. Community partners received printed assets (eg, palm cards and flyers) with the link to the study website and a QR code linked to the study website, as well as social media assets, including graphics sized for multiple social media platforms (eg, Instagram, Facebook, and Twitter [Twitter, Inc]), suggested captions, and potential hashtags.

Upon recruitment, prospective participants were directed to the study website and asked to complete an eligibility screener. Participants who were eligible completed an informed consent process.

To ensure that participants understood the risks that PrEP and participation in this study entail, the informed consent text outlined the risks in a detailed plain language summary. Taking advantage of the functionality available in a web-based setting, comprehension questions were incorporated into the informed consent text; prospective participants could not advance through the document until each question was correctly answered. We received a waiver of parental permission and, therefore, did not require or seek parental consent for minor participants. Participants who correctly answered the comprehension questions and consented to participate were brought to a baseline survey; upon completion, they were randomized into one of the two study arms. Only those who met the eligibility criteria and consented to participate were included in the study.

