Eligible participants were randomized equally between the intervention arm, a web-based telehealth program offering a fully web-based pathway to PrEP, and the control arm, a dynamic web page containing publicly available informational resources about PrEP. We intended to ensure equal allocation of participants across the 4 study areas and equal numbers of adolescent cisgender males and adult transgender females in each study arm (approximately 20 individuals belonging to each subgroup in each study condition).

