### Intervention

Participants allocated to the intervention arm of the study gained access to a web-based telehealth platform called PrEPTECH, which provides PrEP education via self-guided reading material, access to laboratory testing for PrEP eligibility delivered to a participant’s home, and optional SMS text messages or email reminders to aid in medication adherence. PrEPTECH also provides access to telehealth care and PrEP prescriptions for eligible patients asynchronously through a web-based form or synchronously through telephone appointments with the study clinician, an infectious disease physician with expertise in PrEP care licensed in California and Florida. The PrEPTECH intervention tested here is an extension of the piloted PrEPTECH intervention. A brief report on the results of the pilot also discusses the development of the initial intervention by a multidisciplinary team in concert with a previous CAB [42]. It was adjusted to serve a larger group and to be completely web-based. In the second version of PrEPTECH, we incorporated a home laboratory testing kit service, built a platform for offering web-based health evaluations, and developed back-end systems for PrEPTECH to enable the clinical team to review submitted information and communicate with participants. The site was also redesigned for mobile platform compatibility.

All participants who completed at-home laboratory testing and an asynchronous or telephone appointment with the study clinician for whom PrEP was indicated received a prescription for Truvada (emtricitabine, 200 mg or tenofovir disoproxil fumarate, 300 mg). Adult cisgender male participants aged 18 to 27 years received a free 30-day supply of PrEP and subsequently had to pay for PrEP medication through insurance, through patient assistance programs, or out of pocket, should they choose to continue taking PrEP. Adolescent cisgender male participants aged 15 to 17 years and adult transgender female participants aged 18 to 27 years received free PrEP medication for the duration of their 6-month participation in the study because these subgroups were not included in the pilot study of PrEPTECH. Knowing less about the suitability of this intervention for these susceptible populations, the study team opted to provide free medication to them for the duration of the study. PrEPTECH also provides support for signing up for PrEP access programs, prescription transfer, and coordination with community partners.

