If the study clinician was satisfied that the participant was eligible, he would issue a 6-month prescription for PrEP. A free initial supply of PrEP would be filled by Ridgeway Pharmacy, a mail order pharmacy serving both California and Florida, and mailed to a location of the participant’s choice (typically, their home) [42]. For adult cisgender male participants, this initial shipment would be a 30-day supply of PrEP, but for adolescent cisgender male or adult transgender female participants, a 90-day free supply was sent. If a participant tested positive for HIV antibodies or another STI or any significant laboratory abnormalities were found, rather than reporting the results directly to the participant, a synchronous telehealth appointment would immediately be scheduled, and the study clinician would share the laboratory results, provide any necessary counseling, and refer the participant to a community provider for care. These participants would remain included in the study and would still be prompted to take the 90- and 180-day surveys. Then, 30 days after the prescription was sent, participants completed a second medical intake questionnaire, which was reviewed by the study clinician to assess any side effects or challenges encountered in taking PrEP. Participants could also request a synchronous appointment with the study clinician at any time during the study. Furthermore, 3 months (90 days) after enrollment, participants completed a second myLAB Box home testing kit for HIV, syphilis, gonorrhea, and chlamydia, as well as a third medical intake questionnaire, which was reviewed by the study clinician, with similar follow-up procedures as before. Follow-up laboratory tests did not include PrEP adherence measures such as hair sample or blood spot test, as they cannot be performed in the commercial laboratory with which we are working. Communication about steps toward accessing treatment is made through emails and texts, depending on the preferences expressed by the user, which can be indicated on the website itself.

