### Data Analysis

#### Overview

We will report the participant flow through the trial and the results in line with the CONSORT (Consolidated Standards of Reporting Trials) guidelines [48]. All analyses will be carried out following intention-to-treat principles. Data from participants will be allocated to the arm they were initially assigned to, regardless of whether they complete the intervention.

Data analysis will be conducted in SPSS (version 29 or higher; IBM Corp). Descriptive statistics will be calculated to describe the sample at baseline. Binary and categorical variables will be assessed through counts and percentages, and continuous variables will be assessed through means and SDs (medians will be computed for highly skewed variables). To assess baseline equivalence between the intervention and control arms of the study, regression analyses will be performed using age, race, ethnicity, gender, and educational attainment as dependent variables, with intervention condition as the independent variable. The groups will be considered not equivalent at baseline if a given variable differs significantly (*P*<.05) between the intervention arms. Differential and overall attrition will also be assessed using the What Works Clearinghouse recommended approach [49]. We expect ≤5% of the data to be missing; therefore, a complete case analysis is planned with no outcome or baseline imputation. However, if missing data go beyond 5%, then multiple imputation will be explored and run using the *mice package* in R (R Foundation for Statistical Computing) [50].

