The feasibility of PrEPTECH as a telehealth HIV PrEP care intervention for young cisgender men and transgender women who have sex with men will be assessed through a review of the study records. Clinical data will be used to assess loss to follow-up at various intermediate points in the intervention (eg, failure to return at-home laboratory kits or complete asynchronous medical intake forms). Records of clinical communications, written prescriptions, and efforts to assist intervention arm participants and to remind them to complete intervention steps will also be reviewed, with the number of contacts required at various stages calculated.

##### Objective 3

To examine the effects of PrEPTECH on adherence to PrEP, we will examine continuous measures. In each case, a multiple linear regression model will be applied. As described under *Objective 1*, the model will include (1) the intervention group, (2) the number of days between the baseline and follow-up surveys (if applicable), (3) the standard demographics of age at baseline and race and ethnicity at baseline, and (4) a priori demographics and outcome-related covariates that screened positively as candidates for inclusion. Variables will be screened in as described earlier.

The standardized effect size of the intervention on PrEP adherence will also be calculated to determine the magnitude of the effect of the intervention.

##### Objective 4

To examine the moderators of PrEP use, including HIV risk perception, PrEP attitudes, indications of sexual risk, insurance status, and reason for enrolling in the study, we will create multiple logistic regression models with PrEP uptake at 3 and 6 months as the outcome variable, intervention group as the predictor, and the potential moderator as an interaction term. The moderator will be considered statistically significant if *P*<.05.

A more detailed statistical analysis plan will be agreed upon before final analysis.

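### Documented prescription is restricted to undefined "eligible" PrEPTECH participants; on the most natural reading the proportion is close to 100% whatever the programme's reach

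*Protocol article*

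**What the plan says.** Under Secondary Outcomes, PrEP Medication Prescription, the outcome has two stated measures at 3 and 6 months. One is "self-report of having received a PrEP prescription at any point during the intervention", with no restriction by arm or eligibility. The other is "documented medication prescription through study electronic health records (among eligible intervention arm participants only"). The word *eligible* is not defined in that section.

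Elsewhere the protocol uses the word in two senses.

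- **Trial entry.** Recruitment and Randomization states: "Only those who met the eligibility criteria and consented to participate were included in the study". It adds: "Eligible participants were randomized equally between the intervention arm" and the control arm.
- **Clinical clearance for PrEP.** The Intervention section says that all who completed home testing and an appointment and "for whom PrEP was indicated received a prescription for Truvada". It also states: "If the study clinician was satisfied that the participant was eligible, he would issue a 6-month prescription for PrEP".

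The Data Analysis overview states: "All analyses will be carried out following intention-to-treat principles". For feasibility, Objective 2 states: "Clinical data will be used to assess loss to follow-up at various intermediate points in the intervention", and it also plans a review of written prescriptions.

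**The concern.** A proportion informs only if its denominator can contain people who did not have the event. If *eligible* means cleared by the study clinician, the denominator is made up of people for whom the next step is a prescription. Participants who never return a kit, never complete the medical intake form, or are found unsuitable are then in neither numerator nor denominator. A programme that lost most of its participants before clearance and one that lost almost none would report about the same figure.

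This matters because the Limitations section names reliance on self-report as a key weakness and says participants may overstate their PrEP use. Documented prescription is the one named PrEP-access outcome that depends on neither self-report nor survey response, and the study's records can cover every participant randomised to PrEPTECH. Restricting it to people already cleared gives up most of that value.

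**Working it through.** The protocol gives no figure for this outcome, so there is none to reproduce. The sample size calculation concerns self-reported uptake and has no bearing here. The check is a comparison of possible denominators, followed by simple proportions.

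**Step 1: which reading fits the text**

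| Meaning of *eligible* | Support in the protocol | Effect on the proportion |
|---|---|---|
| Met trial entry criteria | Recruitment and Randomization | Denominator is the whole PrEPTECH arm; no effect |
| Acceptable laboratory result only | The Intervention section describes testing as serving PrEP eligibility | Intermediate; intake form and clinician review still follow |
| Cleared by the clinician | The Intervention section, where clearance leads to the prescription | Close to 100% |

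In the trial-entry sense the word would exclude nobody, since everyone randomised already qualifies. In the description of the intervention, where prescriptions are explained, it refers to clearance. The clearance reading is therefore the best supported, but the text does not settle it.

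**Step 2: the arithmetic**

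Let *N* be the number randomised to PrEPTECH, *c* the share cleared and *g* the share of the cleared who are prescribed.

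- Over cleared participants: (*c* × *g* × *N*) / (*c* × *N*) = *g*
- Over all randomised: (*c* × *g* × *N*) / *N* = *c* × *g*

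The first does not depend on *c*, which carries the programme's reach up to clearance.

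**Step 3: inputs**

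- *N*: 229 recruited (Results) with equal allocation (Recruitment and Randomization) gives 229 / 2 = 114.5, taken as 115. Actual arm sizes are not given.
- *g*: about 1, from the two Intervention statements quoted above. A value of 0.9 is shown for sensitivity (assumption).
- *c*: not given. The range 20% to 80% is an assumption.

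**Step 4: results**

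| *c* (assumed) | Cleared, of 115 | Over cleared, *g* = 1 | Over randomised, *g* = 1 | Over cleared, *g* = 0.9 | Over randomised, *g* = 0.9 |
|---|---|---|---|---|---|
| 20% | 23 | 100% | 20% | 90% | 18% |
| 40% | 46 | 100% | 40% | 90% | 36% |
| 60% | 69 | 100% | 60% | 90% | 54% |
| 80% | 92 | 100% | 80% | 90% | 72% |

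The restricted figure is the same in every row; the figure over all randomised moves with *c*. On the laboratory-only reading, the denominator includes the cleared and lies within the randomised, so the proportion falls between the two columns for a given *g*.

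**The case against.** The strongest objection is that the word is undefined. Recruitment and Randomization ties it directly to the arms, and redundancy is weak evidence in a condensed article. It might also exclude only people found unsuitable, leaving those who never returned a kit in the denominator. This stands in part: the near-100% result is conditional on one reading. It does not remove the point, because the article itself states a restriction and the text is either self-fulfilling or ambiguous.

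A second objection is that the denominator of a descriptive secondary measure belongs in the statistical analysis plan, which the protocol says will follow. That would answer a complaint about missing detail. Here a restriction is already written into the outcome definition.

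A reader might also infer more than the documents support.

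- *That the trial cannot show how many randomised participants were prescribed PrEP.* It can. The prescription count is in the study records, the number randomised is known, and Objective 2 already plans to review written prescriptions and losses at intermediate steps. The self-report measure carries no such restriction, though it depends on survey response.
- *That the intention-to-treat commitment is breached.* The tension is mild. The measure exists in one arm only and no between-arm comparison of it is specified, so no randomised comparison is broken. The restriction does sit awkwardly with that commitment, and with the Intervention section's statement that participants with positive tests or significant laboratory abnormalities remain in the study.
- *That limiting the measure to the intervention arm is a fault.* It is not. Study prescription records arise only within PrEPTECH.
- *That the protocol's background figures size the effect.* One telehealth pilot provided PrEP to 20 of 40 enrolled (50%), and another service reports 91% starting among those who completed a video visit. These are different services and different outcomes, so they cannot isolate the effect of a denominator.

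**Conclusion.** The point holds as a minor one. The protocol restricts its record-based prescription measure by an undefined post-randomisation term. On the best-supported reading the proportion is close to 100% by construction and says almost nothing about how far PrEPTECH reached the participants assigned to it. Over the assumed range of 20% to 80% cleared, with all cleared participants prescribed, the restricted figure overstates reach by 80 down to 20 percentage points (100 − 20 and 100 − 80).

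This rests on the clearance reading, on prescription following clearance almost always, and on an assumed share cleared that the documents do not give. If *eligible* means trial entry, there is no distortion; if it means laboratory results alone, the distortion is smaller. One of two stated measures of a secondary outcome is affected. The primary outcome, its analysis and the sample size are not.

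**What to change.** In PrEP Medication Prescription, replace the restriction with a denominator of all participants randomised to PrEPTECH. Count those without a study prescription record as not prescribed through PrEPTECH. The last two words matter, because such a participant may have obtained PrEP elsewhere.

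Report the cleared-only proportion as one step of the feasibility review under Objective 2, with clearance defined in terms of what was completed and reviewed.

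Cross-tabulate documented against self-reported prescription in the PrEPTECH arm. Self-report without a study record may reflect an outside provider and should not be read automatically as over-reporting.

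The change takes a few lines of wording and no new data. Its cost is a less favourable headline percentage if participants are lost before clearance.
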